## Primary and Secondary Outcomes

### Primary Outcome

The primary outcome is the change in gut resistome composition, measured as the difference in total antimicrobial resistance gene (ARG) abundance and diversity between baseline and post-intervention timepoints (2 weeks). This will be quantified using ARG detection by PCR, with results analyzed at the conclusion of the 2-week intervention period. The primary endpoint compares ARG profiles between the intervention groups (Kunun Zaki and Kunun Aya) and the control group using permutational ANOVA (PERMANOVA) with alpha set at 0.05.

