**Research Design**

This is a human intervention study with three arms (1:1:1 allocation ratio) designed to assess superiority of two fermented beverage interventions (Kunun Zaki and Kunun Aya) compared to a control group (no intervention) in modulating the gut resistome. The research follows a quasi-experimental design with participants assigned to different groups by chance to receive either *Kunun Zaki, Kunun Aya*, or no intervention for a 2-week period, followed by a 2-week washout phase. Sample collection occurs at baseline (pre-intervention), at the end of the 2-week intervention period, and at the end of the 2-week washout period.

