### Exclusion criteria

Engaging in any of these during 2 weeks prior to the first sample collection; antibiotic use, intentional intake of probiotic or prebiotic products, presence of gastrointestinal disorders such as diarrhea, inflammatory bowel disease, or irritable bowel syndrome, pregnancy or breastfeeding, alcoholism and drug addiction. For the entire 6 weeks this research will last for, participants will be required to report their daily food and drug intake using an individualised web app developed for this purpose.

Interventions and Comparator

**Intervention 1 - Kunun Zaki:** Participants will consume 500 mL of Kunun Zaki daily for 2 weeks. Kunun Zaki is a traditional Nigerian fermented beverage made from millet or sorghum, supplemented with ginger and cloves as spices.

**Intervention 2 - Kunun Aya:** Participants will consume 500 mL of Kunun Aya daily for 2 weeks. Kunun Aya is a traditional Nigerian fermented beverage made from tiger nuts, prepared through similar fermentation processes as Kunun Zaki.

**Control:** Participants in the control group will maintain their habitual diet without any intervention beverage for the 2-week period.

All participants will be instructed to maintain their usual dietary habits aside from the intervention beverage. Interventions will be delivered by study personnel who will ensure participants receive fresh beverages daily. Adherence will be monitored through daily self-reported logs via the web-based food diary.

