### Statement on invasive sampling

No invasive samples will be collected from the participants.

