### Handling of missing data

Missing data will be documented and reported. For the primary outcome, participants with missing post-intervention samples will be excluded from the per-protocol analysis but included in intention-to-treat analysis using last observation carried forward where appropriate.

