**Ethical Consideration**

This research intends to simulate as close to natural as possible the habitual consumption of the local drinks by the participants, however there remains the risk of possible contamination of prepared drinks during handling by local sellers posing a limited threat to the health of participants (limited because they are used to consuming it ab initio from such sources). Participants will be directed to report any symptom of food poisoning for treatment and discontinuation of research for that participant, as well as other necessary precautions. There is also the concern about handling fecal matter for which participants will be trained on aseptic handling of fecal material, and be provided appropriate materials for same such as sample containers with an attached scoop for easier sample collection, and gloves.

**Confidentiality of data -** The sample bottles would be coded as simple as possible and will not be traceable to any of the volunteers. Names of subjects or identifiers will not be used in any publication or reports from this research. Any personal information collected during the research will be considered and treated as confidential.

**Translation of protocol to the local language -** the protocol will be translated to the local language of the subjects (Hausa) for few persons who may not understand English.

**Beneficience to participants -** After the research, participants will be able to know the positive impact of their diet type on their gut microbiota and by implication food digestion and absorption. Participants will also gain knowledge about antimicrobial resistance genes present in their gut microbiota.

**Non maleficence to participants -** the research will be conformed to professional standard thereby providing no risk to participants.

**Voluntariness --** participation is entirely voluntary

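### The food-poisoning rule, read plainly, ends follow-up and not only the beverage, so a symptom before week 2 costs the primary outcome, mainly in the beverage arms

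*Protocol*

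**What the plan says.** - **Response to symptoms** (Protocol, Ethical Consideration). Participants are told to "report any symptom of food poisoning for treatment and discontinuation of research for that participant". The clause sets no severity threshold and goes on to mention other precautions in general terms. The section calls the threat limited, because participants already drink these beverages from local sellers.
- **Sampling** (Protocol, Research Design). "Sample collection occurs at baseline (pre-intervention), at the end of the 2-week intervention period, and at the end of the 2-week washout period". No early-exit sample is described.
- **Primary outcome** (Protocol, Primary Outcome). It is the change in resistance-gene abundance and diversity from baseline to two weeks, with profiles compared between arms by PERMANOVA at 0.05.
- **Missing data** (Protocol, Handling of missing data). Participants without a post-intervention sample are "excluded from the per-protocol analysis but included in intention-to-treat analysis using last observation carried forward where appropriate". No alternative to LOCF is named.
- **Analysis population** (Protocol, Participants included in analysis). Participants with complete data are used.
- **Control arm** (Protocol, Interventions and Comparator). "Participants in the control group will maintain their habitual diet without any intervention beverage for the 2-week period".
- **Follow-up stated elsewhere.** Secondary Outcomes lists gastrointestinal symptoms and adverse events over the whole study. The Exclusion criteria section asks for daily food and drug reports for all six weeks.

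**The concern.** Stopping a study drink and leaving the study are different events, and the Protocol does not separate them. A participant who becomes ill on the drink should stop drinking it. If that person also stops giving samples, the week-2 measurement is lost for good, and no later analysis plan can recover stool that was not collected.

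The loss would not be random. The hazard named is contamination of the supplied drinks, so cases from it would arise in the Kunun Zaki and Kunun Aya arms and hardly at all in the control arm. A gut illness also bears directly on what the trial measures. The beverage arms could then be represented only by people who stayed well, or partly by imputed values that record no change.

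The rule also sits badly with the Protocol's own safety outcome and six-week diary. Read plainly, it ends reporting for the very people whose symptoms those tools are meant to follow.

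**Working it through.** The Protocol gives no power, effect size, dropout rate or symptom rate (the sample size rests on feasibility and earlier studies), so there is no planned figure to reproduce. The check is mainly one of logic.

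**1. What is lost, by timing of the symptom.** Samples fall at baseline, week 2 and week 4 (the end of washout).
- Symptom before the week-2 sample: the week-2 and washout samples are both lost, leaving baseline only.
- Symptom after the week-2 sample: only the washout sample is lost, and the primary outcome is intact. The drink is taken only in the first two weeks after baseline, so the named hazard would seldom act this late.

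**2. What each analysis does with a participant lost before week 2.**
- Per-protocol: dropped.
- Complete-data rule: dropped.
- Intention-to-treat with LOCF: the only earlier value is baseline, so Y(week 2) is set to Y(baseline). Change = Y(baseline) − Y(baseline) = 0 for every gene and every summary.
- Intention-to-treat with LOCF judged not appropriate: no method is given for keeping the participant.

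**3. Weight of one loss.** With 12 per arm, 1/12 = 8.3% of the arm.

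**4. Effect of LOCF on an arm's mean change.** With k of 12 carried forward, the arm mean is (12 − k)/12 times the mean among those sampled:

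| k | factor |
|---|---|
| 1 | 11/12 = 0.917 |
| 2 | 10/12 = 0.833 |
| 3 | 9/12 = 0.750 |

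The Antimicrobial Resistance Gene Detection section lists 4 classes × 3 genes = 12 targets. If one lost participant's true change was d genes (assumed 1 to 4, in either direction), the arm mean is misstated by d/12: 0.083, 0.167, 0.250 or 0.333 genes.

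These figures describe a mean gene count. They do not give the effect on PERMANOVA, which is the named primary test and was not recalculated.

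**5. Chance that the issue arises at all.** The symptom risk p is an assumption. With 2 × 12 = 24 beverage participants, P(at least one case) = 1 − (1 − p)^24:

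| assumed p | P(at least one of 24) |
|---|---|
| 2% | 38% |
| 5% | 71% |
| 10% | 92% |

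**6. After the fix.** If the week-2 sample is still collected, nothing is carried forward for this reason: k = 0, factor 1.00.

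**The case against.** The strongest objection is that the central step is an inference. The clause is one loosely worded safety line in an ethics section, not a withdrawal rule, and it does not say in terms that sampling stops. The symptom outcome covering the whole study and the six-week diary point towards continued follow-up. This stands in part: it makes the stop-everything reading likely but not certain. Neither of those sections says that a symptomatic participant stays in, though, and the clause names the research, not the drink, as what is discontinued. The sections therefore conflict, and the same sentence resolves the conflict whichever meaning was intended.

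A reader might go further and infer that the primary change will be set to zero. The documents do not support that. The zero arises only in the intention-to-treat analysis, and only if LOCF is judged appropriate. The per-protocol and complete-data routes drop the person instead. What the routes share is that none recovers the outcome.

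A reader might also infer a known dilution of the treatment effect. That is not supported either. The factors above apply to mean gene counts and not to PERMANOVA, the number of losses has no basis in the documents, and the Protocol calls the threat limited.

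Two objections to the remedy are fair. Samples taken after illness or antibiotics may not reflect the beverage, and a sensitivity analysis that excludes post-antibiotic samples loses those participants again. It would, however, sit beside a main analysis that keeps them. Changing this sentence also leaves LOCF in place for week-2 samples missing for other reasons.

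**Conclusion.** The point holds as a fault in the follow-up rule that should be fixed. As worded, the Protocol would most naturally end all follow-up for a participant with any food-poisoning symptom. With no sample between baseline and week 2, a symptom in the beverage period then costs that person's primary outcome. Each such loss is 8.3% of an arm of 12, would fall mainly on the beverage arms and would be related to gut state.

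The conclusion rests on the plain reading of the clause and on the named hazard coming from the supplied drinks. It does not establish that bias will occur, in which direction, or how large it would be in the PERMANOVA. Confidence is medium. The case for acting is that the arms are small, the lost data cannot be recovered and the correction is cheap.

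**What to change.** In the Protocol's Ethical Consideration section, replace the consequence of reporting a symptom with wording such as:

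> treatment and discontinuation of the beverage; the participant continues the diary and symptom reporting and gives the week-2 and washout samples as scheduled unless consent or assent is withdrawn, and is analysed in the assigned arm.

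Use the existing food and drug diary to flag any antibiotic treatment, and add a sensitivity analysis that excludes samples taken after it.

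**Cost.** One sentence of protocol text, plus the remaining diary days and at most two samples per affected participant. Those samples are already planned and self-collected, and the Protocol states that "No invasive samples will be collected from the participants". Protection of the participant is unchanged, since treatment and stopping the drink both remain.

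**Downside.** Some retained samples will reflect partial exposure, illness or treatment and not the full two weeks of beverage. The sensitivity analysis shows how far the result depends on those taken after antibiotics.
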